During the infusion of EN, the patient will be in a 30–40° head-up position. After the administration is finished, the gastric tube will be rinsed with 20 mL of water. The initial volume of the bolus will be 80 mL and will be gradually increased every 4 h according to clinical signs of intolerance and GRV measurements. Signs of intolerance will be considered as abdominal distension or pain, vomiting, diarrhea, and a GRV exceeding 500 mL.

The rate of infusion will be increased according to tolerance and GRV. If there is no sign of intolerance and the GRV is < 250 mL in two consecutive measurements, the volume will be increased by 80 mL/h until the target volume is reached. If intolerance signs are absent and the GRV is 250–500 mL, the current volume of the bolus will remain unchanged. If intolerance signs or a GRV > 500 mL is observed, the volume will be decreased to half until the next assessment of tolerance and GRV.

Measurement of GRV will be performed throughout the entire study period (days 1–5) in 4-h intervals with a 150-mL syringe used for aspiration of gastric content. Volumes lower than 150 mL will be returned to the stomach, and larger amounts will be discarded.

**Table 1 Tab1:** Energy and protein targets

BMI	Energy	BMI	Protein
< 30	25–30 kcal/kg of ABW/24 h	< 30	1.2–2 g/kg ABW/24 h
30–50	11–14 kcal/kg of ABW/24 h	30–40	2 g/kg ABW/24 h
–	–	> 40	2–2.5 g/kg ABW/24 h

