### Outcomes {12}

The primary outcome of the trial is the time from the beginning of the administration of EN to the time at which at least 80% of the target energy is delivered. This will be reported as the day of EN administration. The Kaplan-Meier time-to-event analysis will be used for the analysis of the primary outcome.

Secondary outcomes:
Time from the beginning of the administration of EN to the time at which at least 80% of the target protein dose is delivered. This will be reported as the day of EN administration. The Kaplan-Meier time-to-event method of analysis will be used for the analysis of this secondary outcome.Achievement of the energetic target. This outcome will be aggregated as the proportion of patients who achieve the energetic target during the study period.Tolerance of EN GRV will be aggregated as the proportion with GRV < 250 mL, 250–500 mL, and > 500 mL. Episodes of vomiting will be aggregated as the proportion of patients with any number of episodes of vomiting. Diarrhea stools will be aggregated as the proportion of patients with diarrhea stool > 1 L/day. The need for postpyloric nutrition will be aggregated as the proportion of patients with this need.Incidence of complications of EN. The number of aspiration episodes will be aggregated as the proportion of patients with any number of episodes of aspiration. VAP will be aggregated as the proportion of patients with confirmed VAP.Total serum protein, albumin, and prealbumin concentrations on days 1 and 5. Serum concentrations of protein, albumin, and prealbumin will be aggregated as the mean.ICU and hospital length of stay. ICU and hospital length of stay will be aggregated as the mean. The day of admission and day of discharge will be counted as 1 day.The 28-day mortality will be evaluated with a Kaplan-Meier curve.

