#### Secondary outcomes

The time to reach the protein target will be defined as the number of days from the beginning of the administration of EN to the day at which at least 80% of the planned protein administration has occurred. The trial investigator will estimate that day by analyzing the medical records.

GRVs, episodes of vomiting, the number and volume of diarrhea stools, and the need for postpyloric nutrition will be documented in the medical records and entered in the eCRF by the trial investigator. Diarrhea will be defined as passing of loose stools three or more times per day. The number and volume of stools will be documented in the medical records. Volumes of diarrhea stools exceeding 1 L/day will be reported.

Aspiration of EN is defined as the presence of EN in the airway of the patient. It will be assessed by a nurse during standard airway care and documented in the medical records. The number of aspiration episodes and the incidence of VAP will be entered in the eCRF by the study investigator. Total serum protein, albumin, and prealbumin concentrations on days 1 and 5 will be obtained from the electronic medical records and entered in the eCRF by the study investigator. The ICU and hospital length of stay will be entered in the eCRF by the study investigator after analysis of the medical records. The information on whether the patient is alive or dead on day 28 will be obtained by telephone.

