## Statistical methods

### Statistical methods for primary and secondary outcomes {20a}

For analyses of study data, the intention-to-treat principle will be used.

For analyses of the primary outcome, the Kaplan-Meier curve, log-rank, or Wilcoxon test will be used. Standard descriptive statistics (i.e., number of available values, mean, SD, median, 25% and 75% quartiles, minimum and maximum) will be calculated for continuous variables. Categorical variables will be described by using tables of frequency. Secondary outcome measures will be compared between study groups with the *t* test or Mann-Whitney test as applicable, and the chi-square test will be used for categorical data. Differences in laboratory tests between different days of measurement will be analyzed with paired tests (paired *t* test or non-parametric Wilcoxon test). A Kaplan-Meier curve will be used to demonstrate 28-day mortality. A significance level of 5% will be used for all statistical tests. Confidence intervals will be presented as appropriate.

The data analyses will be performed after completion of the study. Interim analysis is not planned.

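### The GRV outcome gives proportions in three bands without saying whether patients or readings are counted, and the diarrhea outcome leaves out some patients who meet the plan's own definition

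*Protocol article*

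**What the plan says.** **GRV.** Outcomes {12}: "GRV will be aggregated as the proportion with GRV" in three bands: below 250 mL, between 250 and 500 mL, and above 500 mL. Intervention description {11a}: "Measurement of GRV will be performed throughout the entire study period (days 1–5) in 4-h intervals". Nothing in the article says how one patient's series of readings becomes one entry in a band. The other proportions in the same list (energy target reached, vomiting, diarrhea, postpyloric feeding, aspiration, ventilator-associated pneumonia) are all stated per patient; GRV alone is not.

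**Tests.** Statistical methods {20a} opens its rule for these outcomes with "Secondary outcome measures will be compared between study groups with the" t test or the Mann-Whitney test, as applicable, and adds that "the chi-square test will be used for categorical data". GRV is not named, and no method for repeated or clustered readings is given.

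**Diarrhea.** Data collection {18a}, under Secondary outcomes: "Diarrhea will be defined as passing of loose stools three or more times per day". The same paragraph says that volumes above 1 L/day will be reported. Outcomes {12}: "Diarrhea stools will be aggregated as the proportion of patients with diarrhea stool" above 1 L/day. The exclusion criteria {10} call that same volume severe diarrhea. Objectives {7} and the titration rules in {11a} use diarrhea without a volume limit.

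**The concern.** Objectives {7} makes tolerance judged by GRV a key secondary objective, and the abstract names GRV as the main sign that governs feed advancement. Three bands plus a chi-square test look like a complete analysis, but the unit is missing. Two literal readings fail:

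- If readings are the unit, up to 30 correlated values per patient enter the test as if they came from different people.
- If patients are the unit and each is counted in every band where he or she has a reading, the three bands overlap and cannot form one 3×2 table.

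The first failure could produce a false difference in tolerance between the feeding modes. The trial is also unblinded {17a}, so an open choice of unit could be settled after the data are known.

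On diarrhea, a patient who meets the definition at 1 L/day or less shows a sign that the titration rules treat as intolerance, yet enters the outcome table as having no event.

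**Working it through.** The article states no figure for GRV or diarrhea that could be reproduced. Its sample size (122 per arm, raised to 150) concerns the primary outcome and does not bear on this point.

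**Inputs from the article.** Readings every 4 h on days 1–5 {11a}; 150 patients per arm {14}; 5% significance level {20a}.

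**Assumed.** The within-patient correlation of band membership (ICC), for which the article gives no value; the same ICC for all bands and all pairs of readings; the full number of readings for every patient.

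**Step 1, readings per patient.** 24/4 = 6 per day; 6 × 5 = 30. This is a maximum.

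**Step 2, design effect.** DE = 1 + (30 − 1) × ICC.

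**Step 3, true type I error if readings are pooled.** Three bands in two arms give 2 degrees of freedom, with a 5% critical value of 5.991. Under clustering the statistic is inflated by DE, so the type I error is P(χ² with 2 df > 5.991/DE), which equals exp(−5.991/(2 × DE)).

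**Step 4, simulation.** 3,000 trials per ICC, Dirichlet-multinomial readings, no difference between arms, assumed band shares of 80%, 15% and 5%.

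| ICC (assumed) | DE | Pooled readings, formula | Pooled readings, simulated | One worst band per patient, simulated |
|---|---|---|---|---|
| 0.01 | 1.29 | 0.098 | 0.101 | 0.034 |
| 0.05 | 2.45 | 0.294 | 0.291 | 0.044 |
| 0.1 | 3.9 | 0.464 | 0.472 | 0.049 |
| 0.3 | 9.7 | 0.734 | 0.741 | 0.050 |

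Formula and simulation agree. With one band per patient the same chi-square test stays at or below its nominal 5%.

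**Step 5, fewer readings.** If patients gave half the maximum, 15 readings, then at ICC 0.1 DE = 1 + 14 × 0.1 = 2.4 and the type I error is exp(−5.991/4.8) = 0.29. That is smaller than 0.46 but still far above 0.05.

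**Diarrhea.** No arithmetic applies. Set side by side, {18a} defines the condition by stool frequency, while {12} counts patients by stool volume. A patient with three loose stools totalling 1 L or less satisfies the first and not the second. {18a} has both the number and the volume of stools entered in the eCRF, so either measure can be computed.

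**The case against.** The strongest reply is that the article never says readings are pooled and never assigns chi-square to GRV by name. Its neighbours in {12} are all per patient, so a per-patient reading is natural. Several such readings are sound: each patient classed once by highest GRV and compared by chi-square; three separate 2×2 tests of patients with any reading in each band; or each patient's share of readings per band compared by Mann-Whitney, which {20a} allows. The reduction rule may also stand in an analysis plan that is not shown, and the trial calls itself explorative.

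Most of this stands. A reader might infer that the planned GRV comparison is invalid, or that chi-square fails whichever unit is taken. The article supports neither. A reader might also apply the one-degree-of-freedom formula 2 × (1 − Φ(1.96/√DE)) and quote 32% and 53% at ICC 0.1 and 0.3. Those figures are for one band against the rest, not for the three-band comparison. What remains is that the article itself fixes both the GRV summary and the test for categorical data, and as written the two do not determine one valid analysis.

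On diarrhea, the reply is that {12} and {18a} agree: one sentence defines the condition and another sets the volume to be reported. That is a fair reading, and there is no strict contradiction. A reader might go further and infer that most intolerance of this kind is missed, or that events will be few. The article gives no rate of diarrhea by either measure, so neither can be said.

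**Conclusion.** The point holds as one of definition. For GRV, the unit of analysis and the rule for reducing repeated readings are absent from a key secondary outcome whose neighbours all state theirs. The consequence is conditional: only if readings are pooled does the type I error rise to about 10% at ICC 0.01 and 73% at ICC 0.3, with 30 readings for every patient and the ICC assumed. Serious inflation does not need a high ICC, since 0.05 already gives about 29%.

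For diarrhea, the outcome is narrower than the article's own definition and than the objective it serves. Some patients whose diarrhea counts as a sign of intolerance during titration can appear as having none. How many cannot be derived from the document.

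Both parts concern secondary outcomes and leave the primary analysis untouched. They are worth correcting before analysis.

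**What to change.** **GRV.** State the unit in {12} and {20a}. Either class each patient once, by the highest GRV band reached on days 1–5, and compare patients by chi-square; or keep the readings and analyse them with an ordinal GEE or a mixed model clustered on patient. The first is simple but coarser than the readings, and a patient with more readings has more chances of a high one. The second uses all the data but needs its correlation structure written down.

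**Diarrhea.** Report and compare the proportion of patients with diarrhea as defined in {18a}, beside the figure for stool above 1 L/day, and say which of the two is the outcome named in the objectives.

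**Cost.** Analysis wording only. GRV readings and stool counts and volumes are already entered in the eCRF, so no new data are needed.

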### Participant timeline {13}

The schedule of enrolment, interventions, and visits is summarized in Table 3.

### Sample size {14}

Studies focused on the primary target of our study are lacking. However, we have identified several studies comparing bolus and continuous administration of enteral feeding. These studies included small numbers of patients, were conducted in different patient populations, and did not assess the time to reach the nutritional targets as a primary outcome. However, for calculation of the sample size, we hypothesized a difference of 1 day between groups (target being reached on day 2 and day 3, respectively). The alpha was set to 5%, and the power was set to 80%. The estimated sample size was 122 patients per arm. To account for potential drop-out, we increased the sample size to 300 participants in total, with 150 patients in each study arm.

**Table 3 Tab3:** Participant timeline

	Study period							Follow-up
Time point	Screening	D0	D1	D2	D3	D4	D5	D28
Number of visits	1	2	3	4	5	6	7	8
Eligibility criteria	x							
Informed consent	x							
Allocation	x							
Demographic data		x						
APACHE II		x						
SOFA score		x						
Laboratory tests (total serum protein, albumin, prealbumin)		x					x	
Estimation of energy and protein target		x						
Administration of enteral nutrition			x	x	x	x	x	
Assessment of tolerance (diarrhea, vomiting, GRV, postpyloric nutrition)			x	x	x	x	x	
Assessment of complications			x	x	x	x	x	
Assessment of energetic and protein targets			x	x	x	x	x	
Assessment of hospital LOS, ICU LOS, and mortality								x

### Recruitment {15}

Recruitment of patients began in November 2018. During the first 12 months of the study, 787 patients were screened, among whom 100 were allocated to one of the two study arms. Allocation of the last patient is anticipated to occur in November 2021.

## Assignment of interventions: allocation

### Sequence generation {16a}

COINN is a single-center study. The randomization procedure is implemented in an electronic case report form (eCRF) with a randomization ratio of 1:1. The randomization list was generated by the study statistician and implemented in the eCRF by the study data manager.

### Concealment mechanism {16b}

The web-based randomization system ensures allocation concealment.

### Implementation {16c}

The allocation sequence generation is embedded in the trial web site. The study investigator enrolls participants and randomizes them by using the web-based randomization system.

## Assignment of interventions: blinding

### Who will be blinded {17a}

The study staff members and treating physicians and other staff will not be blinded, because of the impossibility of blinding while performing the study intervention. The data management group and statisticians will work with a pseudonymized data set.

### Procedure for unblinding if needed {17b}

Not applicable.

This trial is not blinded.

## Data collection and management

### Plans for assessment and collection of outcomes {18a}

#### Demographic and baseline data

The study will collect demographic and baseline characteristics from medical records and electronic medical records, including age, sex, type of admission, and baseline characteristics. Patient weight will be measured on admission in a standard manner by using a bed-integrated scale; patient height will be measured on admission through a standardized protocol with a tape measure. The patient will lie flat in a supine position. A tape measure will be placed perpendicular to the patient, and the distance from the patient’s heels to the head will be measured.

Conventional scoring systems validated for critically ill patients will be used. Estimation of APACHE II, SOFA, and mNUTRIC scores will be performed by the attending physician and documented in the medical records. Results of laboratory tests will be documented in the electronic medical records and entered by the trial investigator in the eCRF.

#### Primary outcome

The time to reach the energetic target will be defined as the number of days from the beginning of the administration of EN until the day at which at least 80% of the planned EN is administered. The trial investigator will estimate the amount of EN administered by analyzing medical records in which the volume of EN is documented according to institutional standards.

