### Intervention description {11a}

The position of the gastric tube will be verified by measurement of gastric pH or abdominal X-ray. Commercial isocaloric formula with a high content of whey-based protein will be used. To eliminate the effects of formula composition on primary and secondary outcomes of the study, the same enteral formula will be used in all patients included in both study arms. Energetic and protein targets will be estimated according to current guidelines, on the basis of body mass index (BMI) and actual body weight (ABW), as summarized in Table 1 [1]. The energy and protein targets will be determined by the study investigator. The study investigator will provide information to the nurse and attending physician regarding the arm of the study to which the patient was assigned, the time of initiation of EN, and the target rate and bolus volume.

Administration of EN begins no earlier than 6 am and no later than 6 pm if signs of intolerance are absent (see below) and the GRV is below 500 mL. Otherwise, the start of EN will be postponed to the time of the next GRV measurement.

EN will be administered in the first arm (CONT) with continuous infusion via an enteral pump with an infusion time of 18 h per day. During the infusion, the patient will be in a 30–40° head-up position. The initial rate of infusion will be set to 25 mL/h and gradually increased every 4 h according to clinical signs of intolerance and GRV measurements. Signs of intolerance will be considered if abdominal distension or pain, vomiting, or diarrhea occur, and if the GRV exceeds 500 mL.

The rate of infusion will be increased according to tolerance and GRV. If there is no sign of intolerance, and the GRV is < 250 mL in two consecutive measurements, the rate will be increased by 25 mL/h until the target rate is reached. If signs of intolerance are absent, and the GRV is 250–500 mL, the current rate will remain unchanged. If intolerance signs are observed, or the GRV is > 500 mL, the rate will be decreased to half until the next assessment of tolerance and GRV.

The daily dose of EN will be divided in the second arm (INT) into six portions administered in 4-h intervals via an enteral pump. The rate of the enteral pump will depend on the volume of the bolus. To avoid sudden gastric distension, the rate will increase with increasing bolus volume [4]. The rates of the enteral pump for particular volumes of EN are summarized in Table 2.

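### The primary outcome rests on two unblinded judgements, the energy target and the amount delivered: lock the target before randomization and compute the day by program

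*Protocol article*

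**What the plan says.** All references are to the protocol article.

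- **Definition.** Outcomes {12} defines the primary outcome as "the time from the beginning of the administration of EN to the time at which at least 80% of the target energy is delivered" and adds: "This will be reported as the day of EN administration". The Primary outcome section counts days "until the day at which at least 80% of the planned EN is administered". Outcomes {12} thus uses target energy as the denominator, and the Primary outcome section the planned amount of EN.
- **Numerator.** "The trial investigator will estimate the amount of EN administered by analyzing medical records", from records "in which the volume of EN is documented according to institutional standards". For protein, the Secondary outcomes section says: "The trial investigator will estimate that day by analyzing the medical records".
- **Denominator.** Intervention description {11a}: "The energy and protein targets will be determined by the study investigator". Table 1 gives ranges: 25–30 kcal/kg for BMI below 30 and 11–14 kcal/kg for BMI 30–50; for protein, 1.2–2 g/kg for BMI below 30.
- **Order.** Table 3 lists allocation under screening and estimation of the energy and protein targets under D0.
- **Blinding.** Who will be blinded {17a}: "The study staff members and treating physicians and other staff will not be blinded". Under Implementation {16c}, the study investigator enrolls and randomizes.
- **Checks.** Data management {19} has each eCRF reviewed by another team member, who is not said to be blinded.
- **Planned effect.** Sample size {14} assumes a difference of 1 day between groups (day 2 against day 3), with 122 patients per arm before drop-out.

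**The concern.** Both parts of the fraction that defines the event are fixed by people who know the arm. The target is chosen within a range at a visit that Table 3 places after allocation. The delivered amount is then estimated from the chart and compared with a sharp cut on a whole-day scale. Feeding may start at any time from 6 am to 6 pm, and the article does not say whether a day is a calendar day or 24 hours from the start. That adds room for judgement.

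No misconduct need be supposed. If an investigator expects one mode to be tolerated better, a slightly lower target, or a favourable reading of a borderline chart, brings the recorded day forward in that arm. Such an error does not average out and cannot be seen in the final data set. The protein outcome has the same weakness.

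**Working it through.** **1. Where the cut lies (Table 1).** Cut = 0.80 × target.

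- BMI below 30: 0.80 × 25 = 20 kcal/kg; 0.80 × 30 = 24 kcal/kg.
- BMI 30–50: 0.80 × 11 = 8.8; 0.80 × 14 = 11.2 kcal/kg.
- Protein, BMI below 30: 0.80 × 1.2 = 0.96; 0.80 × 2 = 1.6 g/kg.

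An intake of 24 kcal/kg just meets the cut for a 30 kcal/kg target and is 24/25 = 96% of a 25 kcal/kg target.

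**2. Can the choice of target move the recorded day?** Assumptions: perfect tolerance, 1 kcal/mL, boluses rising by 80 mL and rates by 25 mL/h. The text supports two readings of the step rule (an increase every 4 h, or only after two consecutive low readings). I use both and do not choose between them.

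- INT, 60 kg, 4-hourly steps, 25 kcal/kg: target 1500 mL, full bolus 250 mL. Day 1 = 80 + 160 + 240 + 3 × 250 = 1230 mL = 82.0%, recorded as day 1.
- Same patient, 30 kcal/kg: target 1800 mL, full bolus 300 mL. Day 1 = 480 + 3 × 300 = 1380 mL = 76.7%, recorded as day 2.
- INT, 80 kg, 4-hourly steps: day 1 is 73.3% (2000 mL) or 66.7% (2400 mL), so day 2 either way.

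The choice moves some patients and not others.

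**3. How small a volume error moves a patient near the cut?** Four selected targets, perfect tolerance:

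| Arm, day, target | Delivered (mL) | % | 80% cut (mL) | Shortfall (mL) |
|---|---|---|---|---|
| INT day 1, 1680 mL | 80+160+240+3×280 = 1320 | 78.6 | 1344 | 24 |
| CONT day 2, 2250 mL, two-reading steps, no stepping in the infusion pause | 75×6+100×8+125×4 = 1750 | 77.8 | 1800 | 50 |
| CONT day 1, 1400 mL | 25×4+50×4+75×4+77.8×6 ≈ 1067 | 76.2 | 1120 | 53 |
| INT day 1, 1875 mL | 480+3×312.5 = 1417.5 | 75.6 | 1500 | 82.5 |

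The second row depends on its assumption. If steps also accrue during the pause, day 2 is 100×8+125×8+125×2 = 2050 mL = 91.1%, and the cut is passed.

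**4. How often is a patient that close?** Targets from 1000 to 2800 mL in 10 mL steps (assumed range), perfect tolerance. Some day falls within 4 points below 80% for 13% of targets (INT) and 10% (CONT) with 4-hourly steps, and for 6% and 8% with two-reading steps. Within 1 point it is 2–3%. A step-rule simulation with imperfect tolerance (assumed tolerance rates and body weights) put 17–27% of patients within 4 points of 80% on or before their recorded day.

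**5. Effect on the comparison.** The stated 122 per arm cannot be reproduced, because no SD, distribution or event rate is given. As a comparison of means, 122 = 2 × (1.960 + 0.842)² × SD² / 1² implies SD = 2.79 days.

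- *Shift in the mean.* Moving a share f of one arm by one day changes the mean difference by f × 1 day: 0.10 day at 10%, 0.30 day at 30%. With SE = 2.79 × √(2/122) = 0.357, the two-sided false-positive rate is Φ(−1.96 + f/0.357) + Φ(−1.96 − f/0.357): 5.9% at f = 10%, 8.7% at 20%, 13.4% at 30%.
- *Log-rank simulation.* Assumed exponential times, censoring at day 5, 122 per arm, 1,500 trials, Monte Carlo error about 0.6 points near 5%. With a share of one arm recorded a day too early under no true difference, type I error is 5.2% (5%), 5.8% (10%), 5.8% (20%) and 9.8% (30%).
- *Random errors.* Errors of plus or minus one day in 10%, 20% or 30% of both arms, with assumed medians of 2 and 3 days, leave power at 77.2%, 79.4% and 77.6%, against 79.1% without error (Monte Carlo error about 1 point).

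**The case against.** The other side has a good case. Volumes are charted, both arms are fed through an enteral pump, and a second team member reviews each eCRF, so the numerator is not free judgement. A condensed article may leave programming and eCRF layout to fuller documents. Nothing shows that errors would differ between arms, and random errors do little harm.

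Most of this stands and limits the size of the point. It does not remove it. The article states who estimates the amount, who sets the target and in what order, and the reviewer of the eCRF is not said to be blinded. The pump and the chart do nothing to protect the denominator.

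Three stronger readings are tempting and are not supported:

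- *A small volume error equals the planned effect.* One step of the scale is one day, but the planned 1 day is a difference between groups. A mean shift of that size would need every patient in one arm to be moved.
- *Daily totals usually sit next to 80%.* The four examples were selected. Across targets, close calls are occasional.
- *The outcome should be re-expressed in 4-hour units to gain power.* With exponential times, power was 79.1% on whole days and 78.5% on a 4-hour grid, and step-rule simulations showed no consistent gain. A rolling 24-hour sum would also replace the endpoint of Outcomes {12} in a running trial. CONT runs 18 h a day, which is not a multiple of 4 h, and the charting interval is left to institutional standards.

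**Conclusion.** The point holds as a weakness in how the primary outcome is derived, not as an error in the endpoint itself. Two unblinded judgements feed a sharp cut: a target that can place the cut anywhere from 20 to 24 kcal/kg for BMI below 30, and an estimated delivered amount. A patient near the cut can be moved by one day by 24–83 mL in the selected examples, or by the choice of target alone. The danger is differential error between arms. On the log-rank figures it is slight up to about 20% of one arm and material at 30%; the comparison of means shows somewhat more.

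These sizes rest on assumptions outside the article: 1 kcal/mL, perfect tolerance in the worked examples, exponential times with day-5 censoring, an SD inferred from 122 per arm, and hypothetical shares misrecorded. No actual bias is shown. Table 3 gives the order of target setting by visit column only, so knowledge of the arm at that moment is inferred from the column order and the lack of blinding. The change is worth making because it is cheap and keeps the endpoint.

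**What to change.** 1. Record the energy and protein targets in the eCRF before randomization and lock them. Weight and height are measured on admission and randomization precedes the start of EN, so the inputs should be available. Amend Table 3 to match.
2. Enter the charted EN volume for each of days 1–5, and derive by program the first day with at least 80% of the locked target. Do the same for protein.
3. State one day boundary and one denominator, reconciling Outcomes {12} with the Primary outcome section.
4. Keep the whole-day outcome as primary. A finer time scale is at most a sensitivity analysis, where charting allows it.
5. For patients already randomized, tabulate target per kg by arm.

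Cost: up to five daily volumes per patient, one short derivation program, an amendment, and re-extraction of daily volumes for patients already enrolled (100 by 1 December 2019). No extra assessor is needed. Targets already set after allocation cannot be changed retrospectively, so that part of the weakness remains for those patients.
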